### Plans to give access to the full protocol, participant level-data and statistical code

The raw ANNES data is not available for public due to data privacy laws. However, the fully data collection is available from the authors upon reasonable request.

### Recruitment

Patients are recruited by research physicians on the intensive and intermediate care units within the department of neurology, internal medicine and anesthesiology of the University Hospital Tübingen by screening suitable subjects. The recruitment will be monitored in a screening and prescreening log. The duration of the recruitment period is approximately 16 months.

### Assignment of interventions: allocation

Not applicable.

### Assignment of interventions: blinding

Not applicable.

### Data collection and management

**Plans to promote participant retention and complete follow-up**.

Not applicable.

### Data management

All data will be collected in the CRF paper form at first. Authorized clinical staff at the investigational site will enter the data into the electronically CRF (eCRF) using an access controlled, audit-trailed, ICH/GCP compliant, validated system. Entered data will be subjected to plausibility, monitoring and medical review. Implausible or missing data will be queried. Database lock will be performed after completion of data entry, data cleaning and a final data review.

### Confidentiality

All human identifiable data will be stored in anonymized form using a sequential participant identifier. The correspondence between participant identifier and personal identifying information will be kept secure and accessible only where required.

### Data safety and monitoring board (DSMB)

The Data safety and monitoring board (DSMB) – also called data monitoring committee (DMC) is formed by the ZKS Tuebingen, Center for Clinical Studies. It is an independent group of experts in performing clinical trials who monitor patient safety and treatment efficacy data while our clinical trial is ongoing. If necessary, the DSMB can give recommendations to the principal investigators and sponsor of the trial for discontinuation, modification or continuation of the study. Reasons for individual study drug discontinuation or modification might be intolerance to study medication (please see section Trial intervention).

### Plans for collection, laboratory evaluation and storage of biological specimens for genetic or molecular analysis in this trail/future use

Not applicable.

## Oversight and monitoring

**Composition of the coordinating centre and trial streering committee**.

### Biostatistician

[name].

**Composition of the data monitoring committee, its role and reporting structure**.

The data monitoring committee (DMC) is formed by the ZKS Tuebingen, Center for Clinical Studies. The DMC is independent from the principle investigator and sponsor. An interim-analysis is performed after 13 patients, undergoing amantadine treatment for at least 5 days. The study is terminated early if less than 4 successes are observed.

**Adverse event reporting and harms**.

**Safety assessment**.

Adverse events (AE), severe adverse events (SAE) and suspected unexpected serious adverse reactions (SUSAR) will be detected as exploratory endpoints within the study. A serious adverse event (SAE) means any untoward medical occurrence that at any dose:

results in death.is life-threatening.requires inpatient hospitalization or prolongation of existing hospitalization.results in persistent or significant disability/ incapacity.results in a congenital anomaly / birth defect.is medically significant (e.g., suspected transmission of an infectious agent via medicinal product).

Planned hospitalizations or prolongation of existing hospitalization as a result of the following causes need not to be reported as SAE:

drug application.test procedure required in the protocol.hospitalizations for diagnostic measures only.technical, practical, or social reasons, in absence of an adverse event.surgical intervention or other measures and the conditions leading to these measures are not AEs, if the condition leading to the measure was present prior to inclusion into the trial.stay at rehabilitation clinic.

Medical Dictionary of Regulatory Activities (MedDRA)-Coding will be used. All AE, SAE and SUSAR occurring after entry into the study and until day 14 after amantadine treatment (Visit 7) will be recorded. Within 24 h of occurrence, the adverse event has to be reported to the ZKS Tuebingen. The principle investigator or sponsor will determine relatedness of an event to study drug and decides potential termination of Amantadine treatment. The study will monitor for the following adverse events daily during patient examination: epileptic seizure, spasticity, ECG QTc > 480 ms, arrythmia, heart failure and hallucinations.

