### Statistical planning

#### Sample size calculation

The sample size is calculated using the two-stage optimum design of Simon for Phase II trials (see link below or nQuery Sample Size Software). Using this design, we proceed as follows: First we define a favorable true success rate of 40% successes which should lead with 80% power to a successful study. If this rate is 20% or smaller, the study should be with probability of at most 5% (type 1 error, one-sided) successful. We include 43 evaluable patients in the trial. After 13 patients, an interim analysis for futility is performed. The study is terminated early if less than 4 successes are observed. If four or more successes are observed, the study continues with 30 additional patients to recruit a total of 43 patients. According two-stage optimum design the final cut-off are 12 patients. Therefore, the study is successful if at least 13 of 43 patients show an increase of GCS score of at least 3 points (see supplemental Figs. 1 and 2):

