#### Statistical analysis

The study is successful if a total of 13 of 43 patients show success (improvement of at least 3 points on the GCS). Using the two-stage optimum design of Simon for Phase II trials, non-evaluable patients have to be replaced. However, if the necessary number of 13 successes is achieved with less than 43 patients, there will be no early stopping for success. Calculations have been done with a Simon design calculator presented by the NIH on the internet: http://linus.nci.nih.gov/cgi-bin/simonr/cgi_main.

The primary endpoint *improvement of the GCS score from screening up to day 5 of at least 3 points* is analyzed according to the Simon design as described above. The primary analysis population is the per protocol population. This population includes all patients with GCS measurement at day 6 and all patients who died until day 6 (failures). No planned subgroup analyses will be performed. The secondary endpoints (mRS, NIHSS, GOS-E, CRS-R, MoCA after 90 days, RASS and ICDSC) will be analyzed by mixed models with time (categorially coded) as only factor including all measurements up to 3 months follow up. In case of severe violation of normal distribution assumption data will be analyzed by nonparametric tests (Friedmann with including pairwise comparisons using Nemenyis test). No imputation of missing values is planned. P-values will be computed, significances are only “local” in the sense that they are not corrected for multiple testing. The only confirmatory analysis is the one for the primary endpoint.

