#### Interim analyses

After 13 patients, an interim analysis for futility is performed. The study is terminated early if less than 4 successes are observed. If four or more successes are observed, the study continues with 30 additional patients to recruit a total of 43 patients.

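### The monitoring-committee section defines the 13 interim patients by 5 days of treatment, so deaths before then drop out of the futility look yet count as failures at the end

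*Protocol article*

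**What the plan says.** The protocol article describes the interim look in three places.

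- **Sample size calculation** and **Interim analyses**: "After 13 patients, an interim analysis for futility is performed". Fewer than 4 successes stops the trial; otherwise 30 more patients bring the total to 43. Neither section sets a minimum treatment duration. The sample size section adds: "We include 43 evaluable patients in the trial".
- **Composition of the data monitoring committee, its role and reporting structure** (printed under the Biostatistician heading): "An interim-analysis is performed after 13 patients, undergoing amantadine treatment for at least 5 days". The same stopping rule follows directly.

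Two places define who counts at the end. **Statistical analysis** takes patients with a day-6 GCS together with "all patients who died until day 6 (failures"), and has non-evaluable patients replaced. The section on **non-adherence and missing data** also counts deaths until day 6 as failures, and excludes other dropouts before Visit 6.

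**The concern.** A patient who dies on day 3 cannot have had 5 days of amantadine. Under the monitoring-committee wording this patient is not one of the 13. Under the statistical analysis section the same patient is a failure among the 43. A patient whose drug is stopped early but who still has a day-6 GCS is in a similar position: the statistical analysis wording includes the patient, and the 5-day condition does not.

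A Simon design takes its error rates from one sequence of patients and one definition of success. If stage 1 is drawn from completers while the final count includes early deaths, stage 1 has a higher success rate than the population being tested. The look meant to stop an inactive drug then becomes easier to pass. The final number also becomes unclear, because 13 completers plus the early deaths plus 30 more patients is more than 43.

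**Working it through.** **Inputs from the article.** Unfavourable success rate p0 = 0.20, favourable rate p1 = 0.40, power 80%, one-sided type I error at most 5%, stop at 3 or fewer of 13, success at 13 or more of 43.

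**Assumed input.** d, the share of patients who die before completing 5 days. The article gives no figure, so a range of 5, 10 and 20% is shown.

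**Step 1: reproduce the stated design.** Write b(x; n, p) for the binomial probability of x successes in n.

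Probability of stopping early = Σ b(x; 13, p) for x = 0 to 3. At p = 0.20 this is 0.05498 + 0.17867 + 0.26801 + 0.24567 = 0.747, so the chance of continuing is 0.253.

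Probability of final success = Σ b(x; 13, p) × P(Bin(30, p) ≥ 13 − x) for x = 4 to 13. This gives 0.0496 at p = 0.20 and 0.8002 at p = 0.40. A search for the design with the smallest expected sample size at p0 returns the same design, 3/13 and 12/43. The plan's figures are therefore correct, with a margin of only 0.0004 below the 5% limit.

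**Step 2: apply the 5-day condition literally.** Let p be the success rate among all patients, with deaths as failures. Among completers the rate is q = p/(1 − d). Stage 1 is then 13 completers at rate q. The number D of early deaths before the 13th completer has probability C(12 + D, D) × d^D × (1 − d)^13. These deaths enter only the final count.

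Example, d = 10%: q = 0.20/0.90 = 0.222. Early stopping = 0.0381 + 0.1416 + 0.2427 + 0.2543 = 0.677, so the chance of continuing is 0.323.

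**Step 3: final success rate under two readings of the total.** Either the total stays at 43, so that 30 − D patients follow the interim, or 30 patients always follow. The final sum is as in Step 1, with q in stage 1, p in stage 2, and an average over D.

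| Assumed d | q at p0 | Continue at p0 | Alpha, total 43 | Alpha, always 30 more | Power, total 43 |
|---|---|---|---|---|---|
| 0% | 0.200 | 0.253 | 0.050 | 0.050 | 0.800 |
| 5% | 0.211 | 0.286 | 0.053 | 0.058 | 0.831 |
| 10% | 0.222 | 0.323 | 0.056 | 0.067 | 0.859 |
| 20% | 0.250 | 0.416 | 0.063 | 0.094 | 0.902 |

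With the total held at 43, alpha cannot exceed P(Bin(43, 0.20) ≥ 13) = 0.073, its value with no interim look at all. If 30 patients are always added, that ceiling does not apply, because the early deaths come on top of the 43 while the cut-off of 13 stays fixed.

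**Step 4: use one rule at both looks.** Counting deaths as failures among the 13 and among the 43 returns Step 1 exactly.

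**The case against.** The sections that govern the statistics agree with each other. The sample size and interim sections carry no 5-day condition, and the 43 are called evaluable, a set that by the statistical analysis section includes deaths until day 6. The monitoring-committee sentence may be meant as timing only: look once 13 patients have reached the 5-day assessment. This stands so far as it shows an inconsistency and not a settled wrong plan. But even the timing reading does not say whether a patient who died on day 3 is one of the 13, and the sentence sits beside the stopping rule in the section on the committee's role.

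A reader might infer that early failures cannot stop the trial. The article does not support that. A patient who completes 5 days without a 3-point gain is a failure at the interim under every wording. Even on the literal reading, early stopping at p0 is still 71, 68 and 58% for d = 5, 10 and 20%. The monitoring board may also recommend discontinuation on safety or efficacy data, so the futility rule is not the only safeguard.

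A reader might also count every early stop as a mismatch. Most are not: dropouts before Visit 6 other than deaths are excluded and replaced, so they are in neither count. The mismatch comes from deaths, and from a patient stopped early only if a day-6 GCS is obtained and counted.

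Finally, 9.4% should not be quoted alone. It requires enrolment beyond the total of 43 that the article states. At that total the figure is 6.3%.

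**Conclusion.** Wrong as written. The article defines the stage 1 set in two incompatible ways, and the narrower one does not match the final analysis. Followed literally, it breaks the promise that at a success rate of 20% or less "the study should be with probability of at most 5% (type 1 error, one-sided) successful". The margin is so thin that assumed early deaths of 5% are enough under either reading of the total.

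At the stated total of 43 the excess over the 5% limit is modest: 0.3, 0.6 and 1.3 percentage points for d = 5, 10 and 20%. The larger effect is on the futility look, where the chance of continuing with an inactive drug goes from 25% to 29, 32 and 42%. These sizes rest on an assumed early-death share, on a 20% success rate with deaths counted as failures, and on the literal reading. With no early deaths, and no early-stopped patient counted at day 6, the two definitions coincide and nothing is lost.

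**What to change.** Align the sample size, interim analysis and monitoring-committee sections on one rule:

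- The interim takes place when the first 13 patients of the primary analysis population, in order of first dose, have a Visit 6 GCS or have died by day 6.
- Deaths until day 6 are failures at the interim, as they are at the end.
- These 13 are the first 13 of the 43.
- The 5-day treatment condition in the monitoring-committee section is deleted.

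There is no need to count a missing Visit 6 GCS as a failure. That is not the plan's final rule, and adding it would redefine the primary analysis population.

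The cost is wording in the protocol and in the committee's instructions. The sample size and both cut-offs stay, and alpha 0.0496 and power 0.800 are restored. The downside is a somewhat higher chance of stopping at stage 1 than under the literal 5-day wording, which is the chance the design intended.

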### Secondary objectives and endpoints

Secondary objectives are improvement of vigilance/awareness measured via alternative scales using the following: Richmond Agitation-Sedation Scale (RASS), Full Outline of UnResponsiveness (FOUR) Score Coma Scale, Glasgow Outcome Scale – Extended (GOS-E) and Coma Recovery Scale revised (CRSR). Further secondary outcome variables include functional outcome using National Institute of Health Stroke Scale (NIHSS) regarding potential stroke severity and modified ranking score (mRS) in follow-up after discontinuation of medication and after three months. The incidence of complications regarding delirium will be assessed using the Intensive Care Delirium Screening Checklist (ICDSC). The Montreal Cognitive Assessment (MoCA) will assess the neuropsychological outcome. Regarding validity of these measures for determining outcome, please see the paragraph below.

Any adverse event (AE) (any untoward medical occurrence including an abnormal laboratory finding, regardless of its causal relation to the study treatment) will be recorded during the whole study period.

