Women during pregnancy and lactation	-
History of hypersensitivity to the investigational medicinal product	Or to any drug with similar chemical structure or to any excipient present in the pharmaceutical form of the investigational medicinal product
Concomitant therapy with memantine	-
Severe uncompensated heart failure (NYHA IV)	E.g., due to cardiomyopathy or myocarditis
Atrioventricular block (AV block) second-degree and third-degree	-
Known bradycardia (below 55 beats/minute)	-
Known long QT interval (QTc according to Bazett > 420 ms) or recognizable U-waves or congenital QT syndrome in the Family history	-
History of serious ventricular arrhythmias, including torsade de pointes	-
Hypokalemia or hypomagnesemia	-
Concomitant therapy with Budipine or other QT-prolonging drugs	Class IA (quinidine, disopyramide, procainamide) and III (amiodarone, sotalol) antiarrhythmic drugs, antipsychotics (thioridazine, chlorpromazine, haloperidol, pimozide), tri- and tetracyclic antidepressants (amitriptyline), antihistamines (astemizole, terfenadine), macrolide antibiotics (erythromycin, clarithromycin), gyrase inhibitors (sparfloxacin), azole antifungals and other medicines such as halofantrine, cotrimoxazole, pentamidine, cisapride, bepridil
Impaired renal function, measured by glomerular filtration rate (GFR) < 10 ml/min	Impaired renal function will necessitate dose adjustment (see Table 3).

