#### Toxicities

If treatment-related toxicities occur during the study, especially epileptic seizure, spasticity, ECG QTc > 480 ms, or any other suspicious ECG changes or cardial events (e.g., arrythmia, myocarditis, heart failure), drug administration will be terminated immediately. This should be reported as an adverse event.

If hallucinations occur, the dosage will be decreased to 50%. If successful, the administration will be continued with the reduced dosage, otherwise, it will be abandoned entirely. This should be reported as an adverse event.

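### One SAE-reporting exemption also removes AE status from pre-existing conditions that need a measure, has no clause for worsening, and so conflicts with the article's own AE rules

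*Protocol article*

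**What the plan says.** All references are to the protocol article.

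- **Safety assessment (under Adverse event reporting and harms), lead-in to the exemption list:** "Planned hospitalizations or prolongation of existing hospitalization as a result of the following causes need not to be reported as SAE".
- **Same list, the item at issue:** it names surgical interventions and other measures, then says "the conditions leading to these measures are not AEs, if the condition leading to the measure was present prior to inclusion into the trial". The item just before it, on technical, practical or social reasons for a stay, applies only where there is no adverse event. The item at issue has no such qualifier.
- **Same section, recording window:** "All AE, SAE and SUSAR occurring after entry into the study and until day 14 after amantadine treatment (Visit 7) will be recorded". Death and life-threatening occurrences are SAE criteria. Epileptic seizure, spasticity, QTc above 480 ms, arrhythmia, heart failure and hallucinations are monitored daily as adverse events.
- **Secondary objectives and endpoints:** an AE is "any untoward medical occurrence including an abnormal laboratory finding, regardless of its causal relation to the study treatment". Pre-existing disease is not excepted.
- **Toxicities:** for treatment-related toxicities, including seizure, spasticity, ECG changes and "cardial events (e.g., arrythmia, myocarditis, heart failure), drug administration will be terminated immediately. This should be reported as an adverse event". Again there is no exception for prior disease.
- **Table 1:** heart failure is an exclusion only when severe and uncompensated (NYHA IV). Selected rhythm and conduction disorders are excluded, and the ECG must be inconspicuous at entry. Spasticity is not an exclusion.

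**The concern.** The list is introduced as relief from SAE reporting for certain hospital stays. The item makes a different kind of statement: it decides what is an AE at all, and it decides by one fact, whether the condition existed before inclusion. It does not ask whether the measure was foreseen at entry or whether the condition has since deteriorated.

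This matters in this population because every participant enters with serious brain disease and is already in an intensive or intermediate care unit. A need for intervention because existing disease has worsened is therefore a foreseeable event. The Abstract makes the incidence of adverse events an object of study, the Safety assessment section treats AEs as exploratory endpoints, and the data safety and monitoring board follows patient safety during the trial. If staff handle the same event differently according to which sentence they follow, the AE data become incomplete and inconsistent, and nobody reading the AE table could tell.

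**Working it through.** No arithmetic applies. The article states no expected AE rate, so there is no figure to reproduce, and the check is a comparison of the statements.

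1. **Does the lead-in limit the item?** Only partly. The lead-in concerns SAE reporting, while the item's own predicate is that the conditions are not AEs, which is wider. The word for planned in the lead-in can be read as governing hospitalizations alone or prolongation of a stay as well. Since all participants are already in hospital, prolongation is the part that matters, and there the reading is open.

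2. **Does any other sentence supply a worsening clause?** None of the AE and SAE text in the article does so.

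3. **Which situations are in conflict?** Five cases separate them:

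| Situation after inclusion | Exemption item | Other AE text | Conflict |
|---|---|---|---|
| Measure planned before entry, condition stable | Not an AE | Nothing untoward has occurred | No |
| Pre-existing condition worsens, no measure needed | Does not apply | AE by the general definition | No |
| Pre-existing condition worsens and needs a measure | Not an AE, read literally | AE by the general definition; also on the daily list if heart failure, arrhythmia or spasticity; also under Toxicities if treatment-related | **Yes** |
| Worsening is fatal or life-threatening | Lead-in speaks only of hospital stays | SAE by separate criteria | Not clearly |
| New condition arises and needs a measure | Does not apply, because it was not present at entry | AE | No |

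4. **Can the third case occur under the entry criteria?** Yes.
   - The index brain disease is present in every participant.
   - Heart failure below NYHA IV is admitted, and existing spasticity is not excluded.
   - An existing arrhythmia is a narrower example. The ECG must be inconspicuous and several rhythm disorders are excluded, so it would have to be one known from history, outside those exclusions and not visible on the entry ECG.

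5. **Which rule would staff follow?** The article does not say. A specific exemption is often taken to override a general definition. The daily list and the toxicity rule are also specific, and they point the other way. The Toxicities text reaches only events judged treatment-related, so worsening of existing disease judged unrelated rests on the general definition and, for the named events, the daily list.

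**The case against.** The strongest reply is that this is one loosely worded item in a list with limited scope. The lead-in confines the list to hospital stays and SAE reporting, and the item covers only conditions that lead to a measure. The general definition, the recording of all events up to Visit 7, the daily list and the toxicity rule would still bring most deteriorations into the data. The scheduled GCS, FOUR and CRS-R scores would show neurological decline in any case. The full protocol is not shown and may contain a worsening clause.

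Much of this stands and limits the point. A reader might infer three stronger conclusions, and the documents support none of them:

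- *Deterioration of existing disease disappears from the harm data.* Deaths, life-threatening events and the named toxicities remain reportable under text that makes no exception for prior disease.
- *The exemption reaches all 43 participants because all have a brain injury.* Having a prior condition is not the same as having an exempted event. A new bleed or newly developed hydrocephalus is not clearly a condition present before inclusion.
- *The absence of a control arm hides the under-count.* The same exemption would apply in a control arm, which would not reveal it either.

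One part of the reply does not stand. This is not a complaint about detail left out of a condensed article. The article prints a rule on what is not an AE, and that rule contradicts other rules it prints.

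**Conclusion.** The point holds as an internal inconsistency: an item wider than its own lead-in, in conflict with the AE definition, the toxicity rule and the daily AE list. The conflict is confined to one situation, a pre-existing condition that worsens after inclusion and needs a surgical or other measure without being fatal or life-threatening. The consequence there is possible under-recording of AEs.

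Its size cannot be stated as a number. The documents give neither the frequency of such worsening nor the share that staff would treat as exempt. The primary endpoint and the two-stage decision rule are unaffected.

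The conclusion assumes that the printed wording is what staff work from. If the full protocol already has a worsening clause, the problem is reduced to the published text. The correction is worth making because it is cheap and AE incidence is among the things the trial sets out to describe.

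**What to change.** Reword the item so that it matches its lead-in: a stay or its prolongation for a surgical or other measure is exempt from SAE reporting only if the measure was planned before inclusion and the condition has not worsened since inclusion. Remove the statement that the underlying conditions are not AEs. Add one sentence: any worsening of a pre-existing condition after inclusion, including the index brain disease, is recorded as an AE, and as an SAE if a seriousness criterion is met.

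If the full protocol already contains this, align the published wording with it. If it does not, the change needs an amendment. Because recruitment has begun, the amendment should say whether the records of participants already enrolled will be rechecked.

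The cost is one or two sentences, some additional AE forms and possibly a less favourable reported AE rate. No treatment rule, sample size or primary analysis changes.
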